**Table 2 Tab2:**
[figure not shown]
SPIRIT figure

At each follow-up (FU) visit, the research coordinator or research assistant will ascertain patient status (i.e. secondary interventions, adverse events/complications, deaths) and will verify the information within medical records. All adverse events will be addressed to the principal investigator. The patients will be asked to indicate the actual pain level based on the VAS score, if they are currently treated by a physical therapist and if they returned to work. At 6 weeks and 6 months, the range of motion of the wrist will be measured using a goniometer.

Patients will be asked to complete questionnaires relating to disability (qDASH score and PRWE score) and medical consumption, productivity and general health to analyse cost-effectiveness (EQ-5D, iPCQ, iMCQ). Patients will be asked to complete the questionnaires at the ED as well, to generate baseline data.

Plain X-rays of the wrist will be made at the time of presentation in the hospital at the ED, after 6 weeks and 6 months. The X-ray at 6 months will be taken to determine the grade of degenerative joint changes. Time to define the presence of a delayed- or malunion will be at 6 months. Intention-to-treat principle will be maintained.

Both treatment options and used methods of treatment for this type of fracture are well known. Earlier research did not report any (serious) adverse events. All adverse events will be reported by the investigator; severe adverse events will be reported by the investigator to the sponsor of the study without undue delay after obtaining knowledge of the events. We performed an investigator-initiated risk classification: the risk of this study is expected to be negligible. Therefore, no DSMB/safety committee would be necessary. A monitoring audit will be conducted at the start of the study, after inclusion of the first 10 patients and after finishing the inclusion of patients. Also, a line listing of (serious) adverse events will be kept up and reported annually to the Amsterdam UMC Ethical Board.

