This study was initiated to assess whether a period of 1 week of brace immobilisation within non- or minimally displaced DRFs is safe and will lead to an equal functional outcome, earlier return to work, higher patient satisfaction and reduction of health care costs compared to 3 weeks of cast immobilisation. The hypothesis of the study is that 1 week of brace immobilisation is non-inferior to 3 weeks of cast immobilisation.

This randomised controlled trial will provide level 1 evidence on the optimal period and way of immobilisation for non- or minimally displaced distal radius fractures in adult patients. Literature indicates that a shorter period of immobilisation and immobilisation by bracing is safe and might even be beneficial.

This study protocol is based on the ‘DR PIP II: Distal Radius Plaster Immobilization Period II’ study protocol (NL62861.029.17) where 4 weeks versus 6 weeks of cast immobilisation is analysed within displaced and reduced DRFs [21].

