Patients can only participate if the DRF is non- or minimally displaced. They will receive written information and an informed consent form from the attending physician/the clinical investigator/research assistant. When the X-ray taken at the ED showed non- or minimal displacement, informed consent will be signed and eligible patients will be randomised (Fig. 1). An independent research assistant will perform a concealed permuted block randomisation by using a secured computer-generated randomisation schedule after stratification for gender and age. Allocation will be at random in four blocks (Table 1). In total, 1 week of brace immobilisation, if assigned to the intervention group, or 3 weeks of cast immobilisation, if assigned to the control group, will be executed. It is expected that all patients can be included within 1–1.5 year from the start of the study.

**Table 1 Tab1:** Stratification by gender and age

Patient characteristics			Randomisation
List 1	Male	< 30 y.o.a	ABAB AABB ABBA BABA BAAB
List 2	Male	> 30 y.o.a	BAAB BBAA ABAB AABB ABBA
List 3	Female	< 30 y.o.a	AABB ABBA BAAB BBAA BABA
List 4	Female	> 30 y.o.a	ABBA BABA ABAB AABB AABB

*y.o.a.* years of age, *A* 1 week of brace immobilisation, *B* 3 weeks of cast immobilisation

The inclusion and follow-up schedule are visualised in Fig. 2 and Table 2. All patients will be followed for 6 months in total. Assessments will occur at the time of admission at the ED, assessment by phone consult in 1 week after trauma (5–9-day window) in case of inclusion in the intervention group (e.g. 1 week of brace immobilisation), physical assessment in case of the control group (e.g. 3 weeks of cast immobilisation) at 1 (5–9-day window) and 3 weeks (18–24-day window). All patients will be physically assessed at 6 weeks (5–7-week window) and 6 months (5–7-month window) after the start of treatment. After removal of the brace or cast, additional physiotherapy is advised and exercises to train wrist function will be given.

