### Statistical analysis

Data from the demographic data collection and the outcome parameters will be cleaned blindly from the treatment data. Data are presented as mean scores with 95% confidence intervals. Linear regression analysis will be performed if data are not normally distributed.

A blinded evaluation of the trial patient’s functional status will be performed by a research assistant by use of the PRWE and qDASH scores. Blinded radiographic evaluation will be performed the intervention group and the control group. An independent expert will assess the degree of dislocation on an X-ray, blinded from the first assessment. Final blinded analysis of the primary outcome parameters will only be performed after 6-month follow-up.

The analysis of this study will be carried out according to the intention-to-treat principle, i.e. the patients will remain in the group they will be randomly allocated to at the baseline. Analysis of functional outcome will be assessed using repeated-measures analysis of variance (GLM 4) with the time as the within-group factor and the treatment as the between-group factor. The post hoc analysis will be performed on the time of randomisation. Group comparisons at different time points will only be made when the overall repeated-measures tests are statistically significant. All scores will be tested for normality using the Kolmogorov–Smirnov test. Parametric variables will be compared using the Student’s *t*-test, while non-parametric and ordinal variables will be compared using the Mann–Whitney *U* statistic. Nominal variables will be compared across independent groups using the chi-squared test or Fisher’s exact test. Homogeneity of variance will be assessed using Levene’s test.

Baseline characteristics that will be analyses are gender, age, dominancy, fracture side, fracture characteristics, smoking and osteoporosis. The outcome will be tested for normality and according to the outcome mean or median baseline characteristics will be compared.

Primary and secondary outcome measures are functional outcome (PRWE and qDASH), return to work, range of motion, pain, radiological outcome, complications and cost-effectiveness.

Missing data of the PRWE and qDASH score during follow-up can be imputed using multiple imputation based on baseline characteristics

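### The aim is earlier return to work, but the plan describes only a yes/no status, with no contact shared by the arms between week 1 and week 6; a date of return should be recorded and analysed

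*Protocol article*

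**What the plan says.** All references are to the protocol article.

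- **Aim (Background).** The trial was started to assess whether one week in a brace is safe and "will lead to an equal functional outcome, earlier return to work, higher patient satisfaction and reduction of health care costs" relative to three weeks in a cast. Methods/design and the Discussion return to early resumption of work as a reason to prefer the shorter strategy.
- **Outcome (Statistical analysis).** "Primary and secondary outcome measures are functional outcome (PRWE and qDASH), return to work, range of motion, pain, radiological outcome, complications and cost-effectiveness". Return to work does not appear in the outcome list under Methods/design.
- **Data (Sample and selection criteria, text after Table 2).** At follow-up visits patients are asked "if they are currently treated by a physical therapist and if they returned to work".
- **Contacts (Sample and selection criteria).** The brace arm has "assessment by phone consult in 1 week after trauma (5–9-day window) in case of inclusion in the intervention group". The cast arm is seen at weeks 1 and 3. Both arms are seen at 6 weeks and 6 months. No week-3 contact is stated for the brace arm.
- **Test (Statistical analysis).** "Nominal variables will be compared across independent groups using the chi-squared test or Fisher’s exact test". This is a general rule by type of variable. It does not mention return to work, and no time-to-event method is named.
- **Other work data (Methods/design).** The iPCQ is completed at baseline, 6 weeks and 6 months. Absence from work and lost hours enter the indirect costs.

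**The concern.** Whether patients return *earlier* is a question about time. A yes/no answer at a visit shows only that return happened before or after that visit. The arms are treated differently between the end of week 1 and the end of week 3, and no shared contact falls in that period. The next shared question comes at 6 weeks, when many patients in both arms may be back; by 6 months nearly all will be.

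Joining up the visit answers does not repair this, because the grids differ. A cast patient back on day 15 can be recorded at week 3. A brace patient back on day 12 is first recorded as returned at 6 weeks. Taking the first visit with a yes as the time of return would therefore count against the brace.

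At stake is a stated reason for doing the trial. An analysis plan written later can change the test, but it cannot supply dates that were never asked for.

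**Working it through.** **1. The plan's own figure.** No sample size is given for return to work. The 34 per arm in Sample size calculation is for PRWE: 2 × 14² × (1.645 + 1.282)² / 10² = 33.6, rounded up to 34, with a one-sided 5% alpha. It is used below as the number evaluable. A second value, 24 per arm, covers the case where about 70% are in work (0.7 × 34 = 23.8).

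**2. Assumptions, none of them in the documents.** Cast median time to return 3, 4, 5 or 6 weeks; brace median one or two weeks shorter; times exponential, Weibull (shape 2) or lognormal (sigma 0.6). That makes 12 scenarios for each size of gain. The status question is taken to be asked at the week-1 contact in both arms.

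**3. Proportion back by week 6, for median m weeks.**
- Exponential: 1 − 2^(−6/m). For m = 4, 3, 2: 0.65, 0.75, 0.875.
- Weibull, shape 2: 1 − 2^(−(6/m)²). For m = 4, 3, 2: 0.79, 0.94, 1.00.
- Lognormal: Φ(ln(6/m)/0.6). For m = 4, 3, 2: 0.75, 0.88, 0.97.

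**4. Power by simulation** (2000 runs per scenario, two-sided 5%, 34 per arm). Fisher's exact test on status is compared with a log-rank test on exact times, censored at 26 weeks.

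| Medians, cast v brace (weeks) | Distribution | Fisher, week 1 | Fisher, week 6 | Log-rank |
|---|---|---|---|---|
| 4 v 3 | exponential | 4% | 9% | 20% |
| 4 v 3 | Weibull | 1% | 29% | 64% |
| 4 v 3 | lognormal | 0% | 19% | 45% |
| 4 v 2 | exponential | 18% | 48% | 79% |
| 4 v 2 | Weibull | 18% | 73% | 100% |
| 4 v 2 | lognormal | 17% | 63% | 99% |

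A separate simulation with several Weibull shapes gave roughly 46–78% (Fisher, week 6) against 78–100% (log-rank) for 28 v 14 days.

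**5. Across all 12 scenarios, 34 per arm.**
- One-week gain: Fisher 0–11% at week 1 and 3–29% at week 6; log-rank 14–89%.
- Two-week gain: Fisher 2–84% at week 6, above 50% in 7 of 12. At week 1 it is 0–18%, except 67–100% where the brace median is one week. Log-rank 37–100%.
- Month 6: Fisher at most 0.1%.

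With 24 per arm, week-6 Fisher power is 1–21% for one week and 1–67% for two.

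**6. Limit set by the sample size.** With exponential times and 68 returns (2 × 34), Schoenfeld power is Φ(√68/2 × ln HR − 1.96).
- HR 4/3: Φ(4.123 × 0.288 − 1.96) = Φ(−0.77) = 22%.
- HR 4/2: Φ(4.123 × 0.693 − 1.96) = Φ(0.90) = 81.5%.

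Events needed for 80% power are 4 × (1.96 + 0.842)² / (ln HR)², which gives 380 and 66. In the simulations, dates reach 80% power for a one-week gain in only 1 of 12 scenarios.

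**The case against.** The strongest reply is that the article does not fix a faulty analysis. A reader might infer that return to work *will* be tested by chi-squared or Fisher. The text does not say so: the rule is general, and the same section sends non-parametric variables to Mann–Whitney, which would serve if days to return were held. The sentence about asking patients is narrative and does not exclude a date on the form. The assessment schedule is not shown, and a full protocol or analysis plan may say more. That stands, and the missing name of a test is no defect by itself. What remains is that the article describes the item as a status while the aim concerns timing, and the data item has to be settled before the analysis plan can help.

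A reader might also infer that timing is lost altogether. It is not, because the iPCQ collects absence in both arms at the same times. But the article puts those data into indirect costs and nowhere assigns them to the return-to-work comparison.

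Third, return to work is unpowered and absent from the Methods/design outcome list, and the PRWE conclusion does not depend on it. This is also true, and it limits the weight of the point.

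**Conclusion.** The point holds as a mismatch between a timing aim and a status item, made worse by a schedule with no shared contact from week 1 to week 6. Under the assumed distributions, status at shared visits has low power for a one-week gain (3–29% at 6 weeks, 34 per arm). For a two-week gain it generally has less power than dates, except where both are near 100%.

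Two stronger readings go too far. One is that a two-week gain would usually be missed: week-6 power exceeds 50% in 7 of 12 scenarios. The other is that dates bring a large gain in power everywhere. For a one-week gain with exponential times and cast medians of 5 to 6 weeks, the advantage over the better shared visit is about 8 points (15% v 7%, and 14% v 6%).

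Nor would dates make this a powered comparison for one week. Their value lies equally in giving an estimate of how much earlier patients return, with a confidence interval, which a week-6 proportion cannot give. All power figures depend on assumed return times and on the share of patients in work. The change is a cheap improvement to a secondary outcome.

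**What to change.** 1. **Data.** In both arms, at the contacts where return to work is already asked, record the calendar date of first return. State how patients who never stopped work are counted, for example as zero days.
2. **Population.** Patients in paid work at baseline, identified from the baseline iPCQ, provided that item is among those kept.
3. **Analysis.** Days from randomisation to first return, censored at last contact. Kaplan–Meier curves with a log-rank test, or a Cox hazard ratio with 95% CI, stratified by the randomisation strata (gender and age). Label the result secondary and not powered.
4. **Support.** Use iPCQ length of absence as a cross-check. Report yes/no proportions at visits as description only.

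Cost: one form field and a sentence or two in the analysis section; no added visits or patients. The date relies on recall and may be a few days out.

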### Sample size calculation

The primary outcome will be the PRWE score at 6-month follow-up, of which the minimal clinically important difference is 11.5 points. To be conservative, we use a non-inferiority limit of 10.0. The SD of the PRWE is 14.0 [35]. With a power (1 − *β*) of 90% and a type I error (*α*) of 5%, a sample size of 34 patients per treatment group was calculated.

To allow a 10% drop-out, 74 patients will be included, 37 patients per treatment arm. We expect that all patients can be included within 1–1.5 year.

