The PRWE questionnaire will measure the primary outcome (PRWE after 6-month follow-up). In this questionnaire, pain and function are scored on a 0 to 10 scale. The total score can range between 0 and 100, with 0 being the best possible outcome and 100 the worst. The outcome will be tested for normality, and according to the outcome mean or median PRWE after 6 months will be calculated. The mean or median outcome after 6 months in the intervention group (e.g. 1 week of brace immobilisation) will be compared with the control group (e.g. 3 weeks of cast immobilisation). A *t*-test will be used to compare the different outcomes. A *p* value of < 0.05 will be taken as a threshold of statistical significance. To check for clinically relevant results, we will compare the outcomes between the two groups to check whether this difference will reach the minimal clinically important difference of the PRWE of 11.5. Different variables will be compared between the two treatment groups (e.g. 1 week of brace and 3 weeks of cast immobilisation groups). In addition, if possible, a multivariate analysis will be performed, to compare different secondary outcomes to the period of brace or cast immobilisation. Depending on the amount of missing data, we will impute outcomes using multiple imputation based on age, sex, smoking and fracture characteristics. For all analysis, SPSS statistical software (version 28.0) will be used, in which two-tailed *p* value < 0.05 will be considered significant.

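### The 34 per arm fits only a one-sided 5% test, which conflicts with the two-tailed 0.05 and 95% intervals in the analysis section

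*Protocol article*

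**What the plan says.** All design inputs are in the protocol article under Sample size calculation:

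- Margin: "To be conservative, we use a non-inferiority limit of 10.0".
- Variability: "The SD of the PRWE is 14.0".
- Power and error rate: a power "of 90% and a type I error" of 5%, from which "a sample size of 34 patients per treatment group was calculated". One-sided or two-sided is not stated.
- Drop-out: "To allow a 10% drop-out, 74 patients will be included, 37 patients per treatment arm".

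The section states no true difference between the arms.

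Under Statistical analysis, the article says "Data are presented as mean scores with 95% confidence intervals". It names a t-test for the 6-month PRWE, and the closing sentence, which covers every analysis, specifies a two-tailed p: "value < 0.05 will be considered significant". That section does not mention the limit of 10.0. Its only benchmark for size is the minimal clinically important difference of 11.5.

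**The concern.** In a non-inferiority trial only one side of the interval decides the result, so the sidedness of alpha sets both the confidence level and the sample size. Comparing the upper limit of a two-sided 95% interval with the margin is a one-sided 2.5% test. A one-sided 5% test corresponds to a 90% interval. The sample size section appears to use the second convention and the analysis section the first.

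Two things are at stake. Under the stricter convention, the chance of failing to show non-inferiority when the treatments are truly equal is well above the stated 10%. And while the sidedness is open, the error rate behind the primary conclusion could be settled at 2.5% or at 5% after the data are seen.

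**Working it through.** **Inputs.** Margin 10.0, SD 14.0, power 90%, alpha 5%, 37 per arm randomised and 10% loss, all from Sample size calculation. True difference 0 is an assumption; it is the value with which the article's figure reproduces.

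**Step 1: reproduce the 34.** Normal approximation, per arm:

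n = 2 × (SD/margin)² × (z_alpha + z_power)², with 2 × (14/10)² = 3.92 and z_power = 1.2816.

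- One-sided 5%: 3.92 × (1.6449 + 1.2816)² = 33.57, so 34. This matches the article.
- One-sided 2.5%: 3.92 × (1.9600 + 1.2816)² = 41.19, so 42. This does not match.

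Other readings do not give 34 either. A two-sided 5% test to detect a difference of 10 needs 42. Using 11.5 in place of 10 gives 32 (two-sided 5%) or 26 (one-sided 5%). With the noncentral t, one-sided 5% needs 35 and one-sided 2.5% needs 43.

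**Step 2: drop-out.**

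- 37 × 0.9 = 33.3 evaluable per arm, below 34.
- The number needed to keep 34 is 34/0.9 = 37.8, so 38 per arm and 76 in total.
- 34 × 1.1 = 37.4 suggests that 37 came from adding 10% and rounding down.

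**Step 3: power under each convention.** Normal approximation: power = Φ(10 / (14 × √(2/n)) − z_alpha). For n = 34 the first term is 10/3.3955 = 2.945. Subtracting 1.960 leaves 0.985 (83.8%); subtracting 1.645 leaves 1.300 (90.3%). The t column uses the noncentral t with 2n − 2 degrees of freedom.

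| Per arm | One-sided alpha | Normal | t |
|---|---|---|---|
| 34 | 5% (90% interval) | 90.3% | 89.8% |
| 33 | 5% (90% interval) | 89.6% | 89.0% |
| 34 | 2.5% (95% interval) | 83.8% | 82.7% |
| 33 | 2.5% (95% interval) | 82.7% | 81.5% |
| 37 | 2.5% (95% interval) | 86.7% | 85.8% |

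The change of convention costs about 7 points (t: 89.8% to 82.7%). The drop-out rounding costs about 1 (t: 82.7% to 81.5%, or 89.8% to 89.0%).

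**The case against.** The strongest reply is that nothing was miscalculated: at one-sided 5%, 34 is exact and the 90% power is right to within rounding. That stands. A reader might infer an arithmetic error in the 34, but the stated inputs do reproduce it. What is wrong is that the article never says the test is one-sided and then sets a two-tailed threshold.

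A reader might also infer that the trial's real power is simply 82%. The article does not support that without a condition. It nowhere says that a confidence limit for the between-group difference will be compared with 10.0. Its 95% intervals are described for mean scores, and its t-test, as written, tests for a difference. The 82% therefore belongs to one natural rule at the stated level, not to a rule already in the plan. This does not rescue the 90%, however: a two-tailed test of difference does not establish non-inferiority, and one sized to detect 10 points at 90% power would also need 42 per arm.

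On drop-out, the article keeps to intention to treat and allows multiple imputation, so 33 analysed per arm is a simplification. But imputation is left optional and does not fully restore lost information. Even with all 37 per arm fully observed, power at one-sided 2.5% is 86-87%.

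Finally, the stricter alpha does not raise the risk of wrongly declaring non-inferiority, and power stays above 80% on either reading. Both points are correct and limit the consequence. They do not make the two sections agree.

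**Conclusion.** The point holds as an inconsistency between two sections. The 34 per arm matches only a one-sided 5% test, while the analysis section specifies two-tailed 0.05 and 95% intervals.

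- If non-inferiority is judged by the upper limit of a two-sided 95% interval for the difference against 10.0, power is about 83-84% with 34 per arm and 82-83% with 33. The type II risk is then roughly 17-18% instead of 10%.
- If one-sided 5% was intended, power is about 89-90% and only the small drop-out shortfall remains.

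These figures assume a true difference of 0, SD 14.0, and losses that simply reduce the number analysed. The drop-out line is short on its own inputs, but by less than one patient per arm, and is a minor correction.

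**What to change.** State under Statistical analysis how non-inferiority will be decided and at what one-sided level, and carry the same level into Sample size calculation. Either version is coherent:

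1. Non-inferiority is concluded if the upper limit of the two-sided 95% interval for the difference in 6-month PRWE (brace minus cast) is below 10.0, which is one-sided 2.5%. Restate the power as about 82% with about 33 evaluable per arm.
2. The primary non-inferiority test is one-sided at 5%, with a 90% interval, as an explicit exception to the general two-tailed rule. Restate the power after drop-out as about 89%.

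In both cases give the assumed true difference (0), and say that 74 randomised leaves about 33 evaluable per arm.

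The cost is a few sentences and, under the first version, a less favourable power figure. No extra patients are needed to correct the statement. Only if the sponsor wanted to keep 90% power at one-sided 2.5% would the trial grow: 42 evaluable per arm (43 by the t calculation), with 42/0.9 = 46.7 and 43/0.9 = 47.8, so 47 or 48 per arm and 94 or 96 in total. The choice should be fixed before outcome data are examined by arm.
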